### Analysis plan

#### Sample size calculation

A sample size calculator software package (Sample Size Calculator V2.0, Health Services Research Unit, University of Aberdeen) [33] was used to estimate the sample size needed to assess the primary outcome. Validation of the MRS GRACE tool by two clinical pharmacists using de-identified medication charts for 50 residents who were administered medications at least twice per day showed that the number of administration times could be reduced for 23 (46%) residents. As not all recommendations may be implemented by the residential services manager, clinical nurse consultant or GP, we anticipate that the number of administration times could be reduced for 25% of SIMPLER participants receiving the intervention. Allowing for a reduction in administration times for 5% of residents in the comparison group, and assuming 80% power, 5% significance and an intracluster correlation coefficient of 0.1 [34, 35], 22 residents would be required from each facility (i.e. 176 residents). Allowing for a 10% attrition of participants over 4 months, as residents estimated to have less than 3 months to live are not eligible to participate, the SIMPLER study will need to recruit a minimum of 194 residents.

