## Methods

### Design and setting

SImplification of Medications Prescribed to Long-tErm care Residents (SIMPLER) is a non-blinded, matched-pair, cluster randomised controlled trial of a single multidisciplinary intervention to simplify medication regimens using a structured tool. The cluster design was chosen to minimise the potential for contamination associated with nurses and general medical practitioners providing care for a number of residents in the same facility.

Residents will be recruited from eight RACFs between April 2017 and October 2017. Details of participating RACFs can be obtained from the Australian New Zealand Clinical Trials Registry website. Recognising that the average length of stay for permanent residents of aged care facilities in Australia is 35 months [12], participants will be followed for up to 3 years after study entry. In Australia, RACFs (synonymous with long-term care facilities or nursing homes in other countries) provide supported accommodation for people with care needs that cannot be met in their own homes [1]. The RACFs participating in the SIMPLER study predominately cater for residents with high care needs, and are located in metropolitan and rural regions of South Australia. South Australia is the fourth largest state in Australia; it has a population of 1.723 million people [13].

This study is registered with the Australian New Zealand Clinical Trials Registry (ACTRN12617001060336). Details of the World Health Organization (WHO) trial registration data set for the SIMPLER study are provided in Additional file 1. The SPIRIT (Standard Protocol Items: Recommendations for Interventional Trials) checklist for the SIMPLER study is provided in Additional file 2.

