### Primary outcome measure

The primary outcome measure is the total number of charted medication administration times over a 24 hour period for regular medications at 4 months after study entry. This will be determined from medication data extracted by the study nurses. Short-term, nurse-initiated and *pro-re-nata* medications, and nutritional drinks will not be assessed. This outcome will also be determined at 8 and 12 months after study entry to assess the sustainability of the intervention.

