#### Quantitative analyses

Individual-level analyses that account for clustering will be undertaken to determine the relationship between the intervention and study outcomes. Analyses will be undertaken using an intention-to-treat principle; however, sensitivity analyses will be undertaken among residents prescribed medications at least twice per day on a regular basis at baseline, and on a per-protocol basis, in which the intervention group will be restricted to residents for whom at least one medication simplification recommendation was implemented. Mixed models with RACF as a random effect will be utilised to analyse the association between intervention and outcomes. Models will be adjusted for resident characteristics at baseline (including number of medication administration times). Multiple imputation will be used to impute missing covariate values where necessary. Data will be analysed using SAS (SAS Institute, Cary, NC) and the Statistical Package for the Social Sciences (SPSS, Inc., Chicago, IL).

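### The 80% power is calculated for the proportion of residents with any reduction, not for the primary outcome, which is the number of administration times at 4 months

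*Protocol article*

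**What the plan says.** The Sample size calculation section states that a software package "was used to estimate the sample size needed to assess the primary outcome". The effect is expressed as two proportions. For the intervention arm, "we anticipate that the number of administration times could be reduced for 25% of SIMPLER participants receiving the intervention". The comparison figure is introduced with "Allowing for a reduction in administration times for 5% of residents in the comparison group". The remaining inputs are given as "assuming 80% power, 5% significance and an intracluster correlation coefficient of 0.1". The result is 22 residents per facility, 176 in all, raised to 194 for 10% attrition.

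The Primary outcome measure section defines a different quantity: "The primary outcome measure is the total number of charted medication administration times over a 24 hour period for regular medications". The time point is month 4. The abstract agrees with that definition. The Quantitative analyses section specifies mixed models with facility as a random effect and adds: "Models will be adjusted for resident characteristics at baseline (including number of medication administration times").

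No section lists the proportion of residents with any reduction as a primary or secondary outcome.

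**The concern.** The calculation and the analysis concern different variables. A comparison of 25% with 5% needs only the two proportions. A comparison of mean administration times needs a mean difference and a residual SD. Going from one to the other requires an assumed number of times removed per reduced resident and an assumed spread of the count after baseline adjustment, and the article supplies neither.

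The two measures also respond differently to events unrelated to the intervention. If a resident is prescribed something new and gains an administration time, an any-reduction indicator simply records no reduction. The count moves up, which adds residual variance.

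What is at stake is interpretation. A null primary result would be read against an 80% power that was never calculated for it, in a trial with only eight facilities.

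**Working it through.** **Inputs from the protocol article.** 25% v 5%, 80% power, 5% significance (taken as two-sided), ICC 0.1 and 22 per facility (Sample size calculation); eight facilities (Design and setting), one of each pair to each arm (Matching and randomisation). That gives 4 facilities and 4 × 22 = 88 residents per arm.

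**Step 1: the plan's own figure.** For 25% v 5% without clustering, the pooled normal formula needs 49 per arm (59 with continuity correction). The design effect is 1 + (22 − 1) × 0.1 = 3.1, so effective n per arm is 88 / 3.1 = 28.4. Two-sided power for the two proportions at that n is about 56%. With 4 facilities per arm, effective n cannot exceed 4 / 0.1 = 40 however many residents are recruited, which caps power at about 71%. I therefore cannot reproduce 22 per facility at 80% power, even for the proportion comparison.

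**Step 2: detectable difference for the count.** This assumes that ICC 0.1 also holds for the adjusted count.
- SE = SD × √(2 / 28.4) = 0.265 SD
- Large-sample: (1.960 + 0.842) × 0.265 = 0.74 SD
- With 6 df (8 facilities less 2 arms): (2.447 + 0.906) × 0.265 = 0.89 SD

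**Step 3: converting 25% v 5% to a mean difference.** If each reduced resident loses one time, the difference is 0.25 − 0.05 = 0.20. If each loses two, it is 0.40. If nothing else changes, the SD of change in the one-time case is √[(0.25 × 0.75 + 0.05 × 0.95) / 2] = √[(0.1875 + 0.0475) / 2] = 0.34.

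**Step 4: power for the count.** Here z = difference / (0.265 × SD). The SDs are residual SDs, after baseline adjustment, and are assumptions.

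| Difference | Residual SD | Power, large-sample | Power, 6 df |
|---|---|---|---|
| 0.20 | 0.34 | 59% | 45% |
| 0.20 | 0.5 | 33% | 25% |
| 0.20 | 1.0 | 12% | 10% |
| 0.40 | 0.5 | 85% | 71% |
| 0.40 | 1.0 | 33% | 25% |

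The 59% in the first row and the 56% in Step 1 describe essentially the same comparison. They differ because the test of proportions uses a pooled variance under the null.

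**Step 5: what drives the loss.** With no increases in either arm, reductions that are all two times have difference 0.40 and SD 2 × 0.343 = 0.69. The ratio, 0.583, is the same as 0.20 / 0.343, so power is again 59%. A half-and-half mix of one and two times gives 54%. Now suppose instead that 10% of residents in each arm gain one time (an illustration, with reductions of one time). The SD of change rises from 0.34 to 0.49 and power falls to about 34%. Variation unrelated to the intervention is what matters.

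**The case against.** The proportions have a stated basis: the tool validation found that times could be reduced for 23 of 50 residents, so a proportion was the evidence to hand. Nothing in the mismatch biases the trial or alters allocation, the outcome definition or the analysis. Baseline adjustment recovers precision: at a cross-sectional SD of 1.0 and a difference of 0.20, an assumed baseline-to-4-month correlation of 0.7 to 0.8 raises power from about 11–12% to 18–24%. All of this stands, but it does not make the 80% a figure for the count. Nor is it explained by the article condensing a fuller protocol, since the calculation is shown with its inputs and those inputs belong to another variable.

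Three stronger readings are tempting and are not supported:
- A reader might infer that the count and the proportion are equivalent only if every reduction is exactly one time, or only at SD 0.34. Step 5 shows equal power when every reduction is two times.
- A reader might infer that multi-step reductions make the effect much harder to detect. They raise the mean difference as well as the SD, and the mixed case loses only about five percentage points.
- A reader might attribute the whole gap from 80% to the mismatch. The proportion comparison has only about 56% power with these clusters, so part of the gap comes from the cluster arithmetic.

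**Conclusion.** The point holds. The article attaches 80% power to the primary outcome, but the calculation concerns an any-reduction proportion that is not among the listed outcomes, so no stated power applies to the primary analysis. That conclusion rests on the text alone.

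The size of the consequence is conditional. The detectable difference of 0.74 residual SD (0.89 with 6 df) depends on ICC 0.1 carrying over to the adjusted count. The powers, from about 12% to 85% for the cases shown (10% to 71% with 6 df), also depend on assumed residual SDs and an assumed one or two times per reduced resident. The document does not establish that the primary analysis is underpowered by any particular amount: at a difference of 0.40 and residual SD 0.5, the large-sample figure exceeds 80%.

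**What to change.** In the Sample size calculation section, replace the 80% claim for the primary outcome with the minimum detectable difference in baseline-adjusted mean administration times for eight facilities at ICC 0.1. Use the SD from baseline charts pooled across arms without reference to allocation, and a stated range of assumed baseline-to-4-month correlations. The baseline SD alone is not enough, because the residual SD is approximately SD × √(1 − correlation²) and baseline charts cannot supply the correlation.

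State that the 25% v 5% figures refer to any reduction from baseline, and give the recomputed power for that comparison (about 56%). The 80% should not be carried over to it.

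The cost is a revision of wording and one summary statistic from chart data already being extracted. No extra enrolment is needed to make the correction. The stated power will look less favourable.

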### Matching and randomisation

The SIMPLER study will recruit residents from five metropolitan RACFs and three rural RACFs. This includes four metropolitan RACFs with 90–110 beds, a larger metropolitan RACF with 155 beds, two rural RACFs with 40–50 beds each and a rural RACF with 100 beds (all bed numbers are approximate). The RACFs will be paired by the study investigators based on location (i.e. metropolitan or rural) and number of beds. The two smaller rural RACFs will be matched and the larger rural RACF will be matched with the closest metropolitan RACF of similar size. There will be approximately 10% difference in the total number of beds within each pair for two pairs, 20% difference for one pair and 40% difference in the total number of beds for the final pair, owing to the larger size of one metropolitan facility.

One RACF within each pair will be randomised to the intervention group and the other to the comparison (usual care) group. An independent pharmacoepidemiologist will perform the randomisation using the computerised random number generator within SAS (SAS Institute, Cary, NC). Study nurses, residents and staff at each RACF will be blinded to the allocation at the time of resident recruitment; however, owing to the nature of the intervention, it will not be possible to conceal allocation to the intervention or comparison group throughout the study period.

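### On the protocol's own inputs, 22 residents per facility gives about 56–59% power, not 80%; with four facilities per arm at an ICC of 0.1, no number of residents reaches 80% in a two-sided test

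*Protocol article*

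**What the plan says.** All the inputs are printed in the protocol article.

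- **Effect** (Sample size calculation): for the intervention arm, "we anticipate that the number of administration times could be reduced for 25% of SIMPLER participants receiving the intervention"; for the other arm, "Allowing for a reduction in administration times for 5% of residents in the comparison group".
- **Error rates** (same section): "assuming 80% power, 5% significance". Whether the test is one- or two-sided is not stated.
- **Clustering and result** (same section): "intracluster correlation coefficient of 0.1 [34, 35], 22 residents would be required from each facility (i.e. 176 residents".
- **Number of facilities** (Design and setting): "Residents will be recruited from eight RACFs between April 2017 and October 2017". This agrees with 176/22 = 8.
- **Allocation** (Matching and randomisation): "One RACF within each pair will be randomised to the intervention group and the other to the comparison (usual care) group". Four pairs therefore give four facilities per arm.

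The calculation claims no gain from matching or from adjustment for baseline. Under Quantitative analyses, the only random effect named is the facility.

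**The concern.** An ICC of 0.1 is large for a trial with four clusters per arm. Between-facility variation then dominates the standard error of the comparison, and adding residents within the same facilities soon stops helping. A requirement of only 22 residents per facility for 80% power is implausible in that setting.

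This paragraph is the only justification given for the size of the trial. If the claim is wrong, the chance of missing the planned effect is not the 20% that readers will assume but roughly 40–55%. A non-significant result could then be taken as evidence that simplification does not work, in a study meant to inform practice and policy.

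**Working it through.** **Inputs.** p1 = 0.25, p2 = 0.05, power 80%, α = 0.05, ICC = 0.1, m = 22 per facility and k = 4 facilities per arm, from the sections named above. A two-sided test is assumed as the usual default; one-sided results are given under the objection.

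**Step 1: residents per arm without clustering.** The sum of binomial variances is 0.25 × 0.75 + 0.05 × 0.95 = 0.235, and the difference is 0.20.

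- Unpooled: (1.960 + 0.842)² × 0.235 / 0.20² = 46.1
- Pooled (mean proportion 0.15): [1.960 × √(2 × 0.15 × 0.85) + 0.842 × √0.235]² / 0.20² = 48.8
- Pooled with continuity correction: 58.4

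**Step 2: try to reproduce 22 per facility.** The design effect is 1 + (22 − 1) × 0.1 = 3.1.

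| Formula | Needed per arm | Needed in total | Planned in total |
|---|---|---|---|
| Unpooled | 46.1 × 3.1 = 143 | 286 | 176 |
| Pooled | 48.8 × 3.1 = 151 | 303 | 176 |
| Continuity-corrected | 58.4 × 3.1 = 181 | 362 | 176 |

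The stated figure is not reproduced. At 22 per facility, 143/22 = 6.5 to 151/22 = 6.9 facilities per arm would be needed, that is, seven rather than four.

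**Step 3: power of the planned design.** Effective n per arm = 4 × 22 / 3.1 = 28.4. The standard error of the difference is √(0.235/28.4) = 0.0910.

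- Unpooled: Φ(0.20/0.0910 − 1.960) = Φ(0.238) = 59.4%
- Pooled: Φ[(0.20 − 1.960 × √(0.255/28.4)) / 0.0910] = 56.2%
- Noncentral t with 6 df (8 facilities − 2 arms): 45.5%

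Retaining all 194 recruited residents (24.25 per facility) would raise the large-sample figures only to 57.4% and 60.6%.

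**Step 4: the ceiling.** As m grows, k·m / [1 + (m − 1) × ICC] tends to k/ICC = 4/0.1 = 40 per arm. That is below the 46.1–48.8 required. Power at 40 per arm is 71.5% (pooled), 74.2% (unpooled) or about 59% on 6 df. At least five facilities per arm are needed before 80% is attainable at all.

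**Step 5: the ICC that 22 implies.** Solve 88 = n × (1 + 21 × ICC).

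- Pooled: (88/48.8 − 1)/21 = 0.038
- Unpooled: (88/46.1 − 1)/21 = 0.043
- Continuity-corrected: (88/58.4 − 1)/21 = 0.024
- Allowing for 6 df: about 0.015 (power is 83% at ICC 0.01 and 77% at 0.02)

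**Step 6: simulation.** Facility proportions were drawn from beta distributions with ICC 0.1, four facilities of 22 per arm, 100,000 replicates. Power was 59% with known variance and 47% with a facility-level t test on 6 df. With 1,000 residents per facility it was 73% and 62%. Both agree with the formulas.

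**Possible origin.** Entering eight facilities per arm instead of four gives m = 14 (pooled) or 24 (pooled with continuity correction), so that slip does not reproduce 22 exactly either. The document does not show how 22 arose.

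**The case against.** **Sidedness.** The protocol does not say that the test is two-sided. With a one-sided 5% test and no continuity correction, 80% becomes attainable with four facilities per arm, but only at about 89 (unpooled) to 210 (pooled) residents per facility. At 22 per facility, one-sided power is 69–71%. The statement that 80% is unreachable therefore depends on the two-sided test; the failure of 22 does not.

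**Matching and baseline adjustment.** Either could reduce the between-facility variance that matters, and a condensed article may omit a pair term that the full plan contains. That is possible, but the calculation states an ICC of 0.1 and takes no such credit. The pairing is also loose: one pair differs by about 40% in beds and one joins a rural with a metropolitan facility. Even if matching cut the effective ICC to 0.038, a paired analysis on 3 df would have about 50% power.

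**Endpoint.** The primary outcome is the number of administration times, analysed with adjustment for baseline, whereas the calculation concerns the proportion of residents with a reduction. Power for the count could be higher or lower, and the document gives no standard deviation or ICC to compute it. This point stands as a limit: the figures here concern the calculation the protocol presents. It does not support the 80%, because the protocol offers that calculation as the one for its primary outcome.

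**Degrees of freedom.** The protocol does not specify a small-sample reference distribution. The 6 df values are therefore a sensitivity check beside the 56–59%, not a separate error.

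**Conclusion.** The concern holds. On the stated inputs, 22 residents per facility gives about 56–59% power for 25% against 5%, and about 46% allowing for 6 df, where the protocol states 80%. The shortfall is 176 residents against about 286–303 at the same facility size (362 with continuity correction), too large for rounding or choice of formula to explain. It comes from having only four facilities per arm at an ICC of 0.1, so extra residents would not cure it.

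The conclusion assumes a two-sided 5% test, equal facility sizes, the stated ICC with no reduction for matching or covariates, and the binary quantity that the protocol itself powers.

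**What to change.** Replace the 80% claim in the sample size paragraph. Suggested text:

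> *With 8 RACFs (4 per arm), 22 evaluable residents per RACF and an ICC of 0.1, power to detect 25% v 5% of residents with reduced administration times (two-sided 5%) is about 56–59%, or about 46% allowing for 6 df. Power of 80% requires an ICC of about 0.04 or lower (about 0.015 allowing for 6 df).*

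Add that the primary result will be reported with its confidence interval. A sentence saying that a non-significant result will be treated as inconclusive is a reasonable addition, but the correction does not depend on it. If the investigators rely on a gain from matching or baseline adjustment, they should state the reduced ICC they assume and its basis.

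The cost is one reworded paragraph and a less favourable stated power. No residents, facilities or trial procedures change. Recruitment was still open when the article was written, so the correction could be made before analysis.

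### The recruitment minimum of 194 adds 10% to 176 instead of allowing for a 10% loss; 196 are needed to leave 176 (minor arithmetic correction)

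*Protocol article*

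**What the plan says.** All the figures are in the protocol article, under Sample size calculation. The requirement before attrition is that "22 residents would be required from each facility (i.e. 176 residents"). The allowance for loss is worded "Allowing for a 10% attrition of participants over 4 months", and the section links it to the exclusion of residents with a short life expectancy. The conclusion is that "the SIMPLER study will need to recruit a minimum of 194 residents". No inflation formula is given.

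The 176 is 22 × 8, and the number of facilities is confirmed under Design and setting: "Residents will be recruited from eight RACFs between April 2017 and October 2017". Under Matching and randomisation, one facility of each pair goes to each arm, so there are four facilities and 88 required residents per arm.

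**The concern.** The attrition is described as a loss among participants, so the 10% applies to the people recruited. A recruitment minimum built on that allowance should leave at least 176 once 10% of them have gone. The stated 194 looks like 176 with 10% of 176 added, which is a different operation and always gives too small a number.

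What is at stake is whether the stated target is right. The article calls 194 a minimum, so it is the number that recruitment would be judged against, and it falls slightly below the plan's own requirement under the plan's own assumption.

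**Working it through.** **Inputs** (Sample size calculation unless noted)
- Residents required after attrition: 22 × 8 = 176
- Attrition: d = 0.10 over 4 months
- Stated recruitment minimum: 194
- Facilities: 8, four per arm (Design and setting; Matching and randomisation)

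**1. Reproduce the stated figure.** Required number × (1 + d) = 176 × 1.10 = 193.6, rounded up to 194. This matches the article exactly.

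**2. Inflate for a loss among those recruited.** Required number / (1 − d) = 176 / 0.90 = 195.6, rounded up to 196.

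**3. Check forward from the number recruited.**

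| Recruited | Remaining at 10% attrition | Per facility (÷ 8) | At least 176? |
|---|---|---|---|
| 194 | 194 × 0.90 = 174.6 | 21.8 | No |
| 195 | 195 × 0.90 = 175.5 | 21.9 | No |
| 196 | 196 × 0.90 = 176.4 | 22.05 | Yes |

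The smallest adequate total is 196.

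**4. Attrition that 194 can absorb.** 1 − 176/194 = 0.093, or 9.3%.

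**5. Effect on power.** The further inputs are 25% against 5% of residents with fewer administration times and an intracluster correlation of 0.1, all from the same section. The section does not say whether the 5% significance level is one- or two-sided; two-sided is assumed here. The comparison is of two proportions, with each arm's size divided by the design effect 1 + (m − 1) × 0.1, where m is the number per facility. No gain from pair matching is included, because the article states none.
- At 176: m = 22, design effect 3.1, effective size 88 / 3.1 = 28.4 per arm, power 56.2%.
- At 174.6: m = 21.825, design effect 3.0825, effective size 87.3 / 3.0825 = 28.3 per arm, power 56.1%.

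The difference is about 0.1 percentage point. These power values serve here only to size the attrition slip. That they lie well below 80% is a different matter, taken up in the verdict.

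**The case against.** The strongest case against the point is that it is too small to matter. The shortfall is 1.4 evaluable residents out of 176 (0.8%), or two recruits. Power hardly moves, and no part of the design or analysis changes. The figure is also a floor and not a cap, so the trial is free to recruit more. All of this stands, and it is why the point belongs at the lowest severity. It does not make the number right: a floor that misses its own requirement under its own assumption is still misstated.

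It might be said that this is rounding. It is not, because 193.6 had already been rounded up, and no rounding turns 195.6 into 194. Nor does the rest of the article repair it: the multiple imputation under Quantitative analyses is for missing covariate values, not for outcomes of residents who are lost.

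Two stronger readings are tempting, and the article supports neither.
- A reader might take from Design and setting that "the average length of stay for permanent residents of aged care facilities in Australia is 35 months" and infer that 10% attrition is itself too low. The article uses that national average only to justify the length of follow-up. Turning it into a 4-month loss needs an assumed exit rate that the article does not give, for a trial population that excludes residents with a short prognosis or who are medically unstable.
- A reader might infer that 22 must remain in every facility, which would mean rounding up facility by facility. The article sets its recruitment minimum as a total and states no recruitment quota per facility, and its facilities range from about 40 to 155 beds.

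**Conclusion.** The arithmetic slip is real and minor. The stated 194 is 176 increased by 10%; the number that leaves 176 after a 10% loss is 196. At 194 the plan keeps about 175 residents and covers attrition of only 9.3%. The gap is two residents, about 1% of recruitment, with a negligible effect on power.

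This rests on the article's own figures and on one reading: that 10% attrition of participants means 10% of those recruited, which is what the wording says.

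A reader might infer that recruiting 196 would make the sample size sound. That does not follow. The point takes 176 as given, and the standard unmatched calculation above does not reproduce 80% power at 176 from the section's own rates and intracluster correlation. That question lies upstream of the attrition step and is neither caused nor settled by it. Equally, the two-resident shortfall is no ground for calling the trial underpowered.

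**What to change.** Under Sample size calculation, do one of the following:
- restate the recruitment minimum as 196, showing 176 / 0.90 = 195.6; or
- keep 194 and state that it gives about 175 evaluable residents at 10% attrition.

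The first costs two more residents. Recruitment was still open according to the Trial status section, with an anticipated end of 31 October 2017. The second costs one sentence. In either case the wording should make clear that the change concerns the attrition allowance only and is not a fresh justification of the 176.
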